### 4.2 Secondary Objectives

To analyse the effect of LcS on the

- Occurrence of *C. difficile* diarrhoea (CDAD)
- Duration of diarrhoea
- Change in gastrointestinal microbiota (stool specimen analysis)
- Quality of life

- To determine if malnutrition (undernutrition) is a risk factor for AAD and CDAD
- To determine if use of proton pump inhibitors (PPI) is a risk factor for AAD and CDAD.

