#### 5.1.2 General Exclusion Criteria

- Re-recruit patient (ie, only patients recruited for the first time are allowed)
- Antibiotic use in the 30 days prior to the study product first administration apart from a single dose of prophylactic given more than 14 days before the study product's first administration.
- Diarrhoea within the preceding 7 days prior to commencement of intervention
- Bowel pathology that could result in diarrhoea
- Recent bowel surgery
- Infective endocarditis
- Active inflammatory bowel disease
- Pancreatitis
- Regular probiotic use
- Any illness requiring ITU intervention or systemic sepsis
- Immunosuppression
- Nil-by-mouth status for any reason
- Non-functioning gut (Include those on Parenteral Nutrition)
- Known cows' milk protein intolerance
- Psychiatric or cognitive conditions that may interfere with the study
- Patients incapable of providing informed consent due to a mental incapacity
- Patients unlikely to comply with study requirements
- Pregnant or breastfeeding women
- Prisoners

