### **5.3 Informed consent procedure**

The study team will be contacted by the ward and informed when a patient is to start / or has been started on antibiotic therapy for an infection. A member of the research team will approach the subject and provide the participant information sheet and if the subject shows an initial interest, the study coordinator will explain (1) the purpose of the study, (2) the procedures, (3) the risk / benefits, (4) alternatives to participation, (5) and the confidentiality. At this stage, the study coordinator will emphasise that the current feasibility study does not influence the provision of other healthcare services delivered by the specialised services. Candidate will be offered up to 24 hours to consider participation in the current study and will have the opportunity to ask any study-related questions that arise. Should the patient wish to go ahead with the study, consent will be specifically sought for 1. participation in this study and 2. the use and storage of de-identified data for the current research project.

Patients able to consent for themselves will be asked to sign an informed consent form. A witness will be asked to sign on behalf of those patients unable to sign the form due to physical disabilities. After obtaining informed consent, patients will be allocated (SM xx, Os xx, or Ts xx depending on sites), undergo their baseline assessments and offered Yakult or placebo (according to randomisation result) within 48 hours of commencing their antibiotic. The study drink will then be given once a day at the drug round in accordance with the protocol.

A master ID log will be maintained at each site.

The participant will be informed about their right to withdraw from the study at any time and for any reason without sanction, penalty, or loss of benefits to which the patient is otherwise entitled. A register will be kept of all patients who withdraw from the study. The reason for consent withdrawal will be documented along with the following core patient characteristics: age, gender and level and severity of spinal cord injury.

A copy of the signed Informed Consent Form - approved by the Research Ethics Committee - will be retained at the investigational site along with other investigational forms. A copy of the signed informed consent form will be placed into the patient's medical record, patient file (original) and a copy will be handed over to the patient.

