### **5.5.3 Randomisation: blinded treatment. Group allocation**

Following enrolment, participants will be randomised to either the intervention or placebo group. Random assignment will be performed by [name]. To ensure balanced groups for interim safety analysis, we will utilise a block randomisation technique, with permuted blocks of 30 for each study centre and for previous antibiotic use (15 to group 1 and 15 to group 2 per block), until sample size criteria are met.

Participants, medical and nursing staff, and investigators (study field staff) will also be blinded to allocation for the probiotic or placebo. The study code will be kept by the study statistician who will have no clinical role and no contact with patients.

After the study's opening assessment is completed (section 5.5.2), the randomisation list will be forwarded to the product distributor (Yakult Europe BV) by the Trial Statistician. Yakult Europe B.V. will arrange for product packs to be delivered, each with a sticker / code specific for each participant. This will ensure the hospital researchers are blinded to verum or placebo.

The placebo will be in identical packaging and of similar appearance and taste. The placebo has been used in several European studies and proven to be effective for blinding purposes.

Study field staff will be unaware to which group the subjects are assigned. See Appendix 5 for the decision tree outlining recruitment and randomisation of subjects. The study code will be kept by the study statistician who will have no clinical role and no contact with patients. Communications via electronic means will be encrypted (AES256), as per Instauration's Standard Operating Procedure.

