## **7.4 Statistical analysis**

We will analyse the data using intention-to-treat principle. Fisher's exact test and  $\chi^2$  test will be used to compare rates of diarrhoea, as well as rates of AAD and CDAD. Relative risk and the number needed to treat, both with 95% confidence intervals, will be used to describe the treatment effect of probiotic. Logistic regression will be used to establish which factors influence the occurrence of diarrhoea. Continuous outcome measures will be analysed utilising ANCOVA (controlling for baseline scores and existing group differences) and multiple regression analyses ( $p<0.05$  critical value; sample size covers this analysis to a sufficient power level).

To reduce the bias implicit in utilising only complete cases, multiple imputation procedures for the laboratory data will be used using the SPSS (SPSS version 15, Inc, Chicago, IL) Markov Chain Monte Carlo multiple imputation function to produce 10 imputed datasets. These will then be analysed as normal; thereafter standard multiple

imputation procedures were used to combine the multiple scalar and multivariate estimates quantities.

To minimise confounding factors with respect to incidence of AAD and CDAD, stratification will be performed at the time of recruitment according to the antibiotic background (i) patients who have not previously received antibiotics in the 30 days prior to administration of intervention ('antibiotic-naïve') and (ii) patients who had been given a single antibiotic treatment for prophylactic purpose >14 days before first administration of intervention ('prophylactic-antibiotic').

In addition, a sub-group analysis will be performed on both treatment arms to analyse the following for association with AAD/CDAD occurrence: (i) risk of undernutrition, (ii) use of proton pump inhibitor, (iii) age  $\geq 65$  years and (iv) those receiving study drink within 24 hrs vs 48 hrs of first dose of antibiotics.

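### The planned sub-group analysis of drink timing (24 v 48 hours) targets association with AAD/CDAD, which cannot show whether the LcS effect depends on timing and can be mistaken for evidence that it does

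*Protocol*

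**What the plan says.** Section 7.4 of the protocol announces that "a sub-group analysis will be performed on both treatment arms to analyse the following for association with AAD/CDAD occurrence". Four factors follow: risk of undernutrition, PPI use, age 65 or over, and "those receiving study drink within 24 hrs vs 48 hrs of first dose of antibiotics". The only other analysis of factors in that section is a regression: "Logistic regression will be used to establish which factors influence the occurrence of diarrhoea". Neither sentence names a comparison of the LcS effect between levels of a factor.

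Section 4.2 gives two of the four an objective, in both cases prognostic: "To determine if malnutrition (undernutrition) is a risk factor for AAD and CDAD" and "To determine if use of proton pump inhibitors (PPI) is a risk factor for AAD and CDAD". Age and drink timing have none.

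Drink timing is not randomised. Under section 5.3 it depends on when the ward notifies the team and on the consent process, in which "Candidate will be offered up to 24 hours to consider participation in the current study". Section 5.5.3 stratifies by "permuted blocks of 30 for each study centre and for previous antibiotic use", and timing is not among these factors.

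**The concern.** Undernutrition, PPI use and age are patient characteristics, and whether they go with more diarrhoea is a sensible question in its own right. Drink timing describes how the study product was delivered. It bears on LcS only if the LcS-placebo difference is larger or smaller in early starters. A test of association between timing and AAD has a different null hypothesis, namely that early and late starters have the same AAD risk.

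That null can be false with no timing effect of LcS at all. Early and late starters select themselves and may differ in prognosis. Eligibility adds a further, smaller route: section 5.1.2 excludes "Diarrhoea within the preceding 7 days prior to commencement of intervention", so a later starter has to stay free of diarrhoea for longer after the first antibiotic dose. Either route would act in both arms. The placebo arm is the natural control for this, but an association target does not use it as one.

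At stake is a secondary message about when the product should be started, drawn from a difference that would be equally present on placebo.

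**Working it through.** **Inputs from the protocol (section 7.2).** AAD rates 56.3% and 38.4%, alpha 0.05, power 90%, 162 per group, 180 per arm after 10% dropout. The text attaches 56.3% to PPI users; I use it as the placebo-arm rate, as the calculation itself does.

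**Reproducing the stated figure.** Two-sided, pooled variance, no continuity correction, mean rate 0.4735:

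n = [1.960 × √(2 × 0.4735 × 0.5265) + 1.2816 × √(0.563 × 0.437 + 0.384 × 0.616)]² / 0.179² = (1.384 + 0.890)² / 0.03204 = 161.4, so 162. Then 162 / 0.90 = 180. Both figures reproduce. The protocol gives no figure for the sub-group analysis.

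**Assumptions not in the protocol.** Late starters have 1.5 or 2.0 times the odds of AAD of early starters, equally in both arms, so the LcS odds ratio is the same in early and late starters. Half of patients start early (70% as a variant). Early rates are set so that each arm keeps its planned overall rate.

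Cell rates, half early (81 per cell):

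| Late v early odds ratio | Placebo early / late | LcS early / late |
|---|---|---|
| 1.5 | 51.3% / 61.3% | 33.6% / 43.2% |
| 2.0 | 47.9% / 64.7% | 30.3% / 46.5% |

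**Hand check of the pooled test.** For odds ratio 1.5, the rates averaged over arms are 42.5% early and 52.2% late, a difference of 0.0975. SE = √(2 × 0.4735 × 0.5265 / 162) = 0.0555, z = 1.76, and the chance of significance is Φ(1.76 − 1.96) = 42%. For odds ratio 2.0 the difference is 0.165, z = 2.98, and the chance is Φ(1.02) = 85%.

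**Simulation** (200,000 trials per case, 162 per arm, two-sided 5%, no timing effect of LcS in any row):

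| Early share | Odds ratio | Pooled association | LcS arm alone | LcS significant, placebo not | Interaction |
|---|---|---|---|---|---|
| 50% | 1.0 | 5% | 5% | 5% | 5% |
| 50% | 1.5 | 42% | 24% | 18% | 5% |
| 50% | 2.0 | 86% | 56% | 24% | 5% |
| 70% | 1.5 | 37% | 22% | 17% | 5% |
| 70% | 2.0 | 79% | 52% | 26% | 5% |

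Setting the prognostic difference on the risk scale instead (10, 15 or 20 points, 50% or 70% early) gives 38–44%, 71–78% and 92–96% for the pooled test. The interaction test stays at about 5%.

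**Power of the interaction test.** Take an interaction as large as the whole planned effect: LcS lowers AAD by 17.9 points in early starters and by nothing in late starters. With 81 per cell, the variance of the difference between the two risk differences is (3 × 0.2460 + 0.2365) / 81 = 0.01203, so SE = 0.1097. Then 0.179 / 0.1097 = 1.63 and power = Φ(1.63 − 1.96) = 37%. Across 50% or 70% early, and with the effect split 26.9 v 9.0 points instead, power is 32–38%. For a 35.8-point interaction it is 86–92%.

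**The case against.** The protocol announces an association and nowhere says that it would read one as a timing effect of LcS. A reader might infer that such a misreading is built into the plan. The text does not support that; it leaves the door open and no more.

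A reader might also extend the criticism to all four factors. That fails for undernutrition and PPI use, where association is the stated objective, and for age, where it is a fair prognostic question as written.

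The phrase about both treatment arms may mean an arm-by-arm analysis, in which a prognostic difference would tend to show on placebo too. This helps less than it seems. Setting one arm's p-value beside the other's is not a test of their difference, and LcS alone is significant in 17–26% of the trials simulated with a prognostic difference. The arm-by-arm reading does, however, remove a further charge that one might make, that a real timing effect would be missed. Take LcS with twice its planned log-odds effect in early starters and none in late starters, and early starters with 1.5 times the odds of AAD. The pooled test then has 25% power, but the LcS-arm test has 89%, the same as the interaction test.

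The protocol gives no evidence that start time is related to prognosis. The eligibility route would lower late starters' risk, not raise it as in the simulation. It covers about one extra day against follow-up to 30 days after antibiotics, and it could partly offset other differences. The simulated sizes are therefore illustrations.

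Finally, interaction terms are often left to the SAP, which is not shown. The point does not rest on a missing term. It rests on the target that section 7.4 does state, which an SAP following that section would inherit.

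**Conclusion.** The point holds for drink timing only. An association between timing and AAD, whether pooled or read arm by arm, cannot show that the LcS effect depends on timing, and a purely prognostic early/late difference can be mistaken for such a dependence. With 162 per arm, half starting early and an assumed prognostic odds ratio of 1.5 or 2.0 common to both arms, the pooled test is significant in about 42% or 86% of trials. LcS is significant while placebo is not in about 18% or 24%. An interaction test is significant in 5%. The odds ratio and the early share are not in the protocol; with no prognostic difference the pooled test keeps its 5%. Severity is minor, because neither the primary nor any listed secondary outcome is touched.

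**What to change.** In section 7.4, keep the association analysis for undernutrition, PPI use and age, in a logistic model that includes treatment arm. For drink timing (up to 24 hours v more than 24 to 48 hours), replace it with a logistic model containing arm, timing and the arm-by-timing interaction. Report the LcS-placebo relative risk with 95% CI within each level and the interaction p-value, and label the analysis exploratory. Do the same for age only if effect modification by age is intended. Add a sentence that no claim about timing of LcS will rest on an association within one arm or pooled over arms.

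The cost is a change of wording and one model term, with no new data. The drawback is power: at 32–38% for a 17.9-point interaction, the analysis will rarely support a timing claim, and a non-significant interaction must not be read as showing that timing does not matter.

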#### 5.5.2 Study procedure: opening assessments

After having obtained informed consent (1x copy to patients; 1x copy in medical notes; 1 x original in the investigator site file), basic patient's clinical characteristics and baseline measurements, as outlined on the Case Report Form (CRF, see [Item 12.1](#)), will be collected. No intervention will be administered prior to the completion of the study opening visit.

- Baseline demographics and clinical data
- Record use of medications (including use of antibiotics, laxatives, anti-diarrhoeal agents, proton pump inhibitors, H2 blocker)
- Nutrition risk scores – Spinal Nutrition Screening Tool (Wong et al, 2010, 2012)

- Quality of Life evaluation – WHO-QoL BREF ([http://www.who.int/substance\\_abuse/research\\_tools/en/english\\_whoqol.pdf](http://www.who.int/substance_abuse/research_tools/en/english_whoqol.pdf))
- Bowels function measures – stool type, duration of diarrhoea  
Definition of diarrhoea: two or more loose stools, Bristol Stool Scale (O'Donnell LD, 1990) type 5 or above.  
Constipation: using Rome III criteria: Functional constipation ([http://www.romecriteria.org/assets/pdf/19\\_RomeIII\\_apA\\_885-898.pdf](http://www.romecriteria.org/assets/pdf/19_RomeIII_apA_885-898.pdf)) (Drossman DA, 2006).
- Stool Specimen analysis (Kubota *et al.* 2014)  
One sample will be taken, frozen and stored frozen and then sent to YHER for TaqMan PCR analysis of toxigenic *C. difficile*. This analysis will be dependent on available resources at YHER. Further microbial analysis may also be done. This will be in the participant information sheet and on the consent form.

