## **7.2 Sample size considerations**

Based on pilot data, this study aimed to find a difference of 17.9% in the proportion of patients with diarrhoea in two groups, (i) those on proton pump inhibitors – 56.3% and (ii) those on LcS – 38.4%. With  $\alpha=0.05$  and power of 90%, we estimate a sample size of 162 per group. After accounting for dropouts at 10% (across the length of the trial) this will require 180 per arm (total  $n=360$ ).

This sample size calculation is based on data from a single study site, but it seems reasonable to extrapolate the findings to other UK SCI centres. Therefore we aim to recruit 360 (180 per arm) in the proposed trial.

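### Age is split at 65 years and drink delay at 24 hours without justification; the planned logistic regression should use the underlying values, with the cuts kept for description

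*Protocol*

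**What the plan says.** Protocol section 7.4 describes two analyses that bear on risk factors.

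- A regression: "Logistic regression will be used to establish which factors influence the occurrence of diarrhoea". The section does not list the factors or say how they are coded.
- After that, and as an addition to it, a sub-group analysis in both arms for association with AAD/CDAD. Its list runs "i) risk of undernutrition, (ii) use of proton pump inhibitor, (iii) age", the age item being 65 years or over. The fourth item compares patients who had the study drink within 24 hours of the first antibiotic dose with those at 48 hours.

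Age and drink delay are therefore explicitly split in two, and no section gives a reason for either cut. Nutrition is different: section 7.4 names it only as a risk, with no cut-off and no number of groups. Section 5.5.2 collects it as "Nutrition risk scores" from the Spinal Nutrition Screening Tool (SNST). Section 4.2 makes it a secondary objective: "To determine if malnutrition (undernutrition) is a risk factor for AAD and CDAD". Neither age nor drink delay appears in any stated objective.

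**The concern.** A cut at 65 treats patients of 64 and 66 as different, and patients of 20 and 64 as the same. A cut at 24 hours does likewise for delay. If risk changes gradually, a two-way comparison is a weaker test than one that uses the recorded value, and a null sub-group result may reflect the cut and not the factor. The loss grows as one group becomes small, which would matter for age if few inpatients are 65 or over.

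The timing item is also loosely worded. Anyone who has the drink within 24 hours also has it within 48, so as written the groups are not exclusive. Section 5.1.1 already limits the first drink to 48 hours, so 0–24 against more than 24–48 hours is probably meant.

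At stake is how supportive risk-factor results are interpreted, not the trial's main conclusion.

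**Working it through.** **The plan's own figure.** Section 7.2 uses 56.3% and 38.4% and states "power of 90%, we estimate a sample size of 162 per group". With a two-sided α of 0.05, pooled variance and no continuity correction:

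n = [1.96·√(2 × 0.4735 × 0.5265) + 1.2816·√(0.563 × 0.437 + 0.384 × 0.616)]² / 0.179² = (1.384 + 0.890)² / 0.03204 ≈ 161.4, hence 162.

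Then 162/0.9 = 180 per arm. Both figures reproduce. The protocol does not state sidedness; one-sided gives 132, and two-sided with continuity correction gives 173. For the checks below, n = 2 × 162 = 324 evaluable patients, and the overall diarrhoea rate is (56.3 + 38.4)/2 ≈ 47%.

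**Information kept by a two-way split.** For a linear effect on the log-odds that is not large, the share of information kept is the squared correlation between the factor and its split indicator.

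*Age, assumed normal, share s aged 65 or over.* Kept = φ(z)² / [s(1 − s)], where z cuts off the upper share s. At s = 15%, z = 1.036 and φ(z) = 0.233, so kept = 0.0544/0.1275 = 0.426. Power after the split is given for a factor that would have 80% power as a continuous term: Φ[(1.96 + 0.84)·√kept − 1.96].

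| Share ≥65 (assumed) | Kept | Loss | Effective n of 324 | Power after split |
|---|---|---|---|---|
| 50% | 0.637 | 36% | 206 | 61% |
| 30% | 0.576 | 42% | 187 | 57% |
| 20% | 0.490 | 51% | 159 | 50% |
| 15% | 0.426 | 57% | 138 | 45% |
| 10% | 0.342 | 66% | 111 | 37% |
| 5% | 0.224 | 78% | 73 | 26% |

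Logistic simulations with n = 324, about 47% events and an odds ratio of about 1.38 per SD (assumed, chosen to give about 80% power) agree within simulation error. Two sets of runs gave 80–83% power for the continuous term, against 64%, 57–60%, 51–56% and 42–47% after a split with 50%, 30%, 20% and 15% above the cut. One set used 600 runs per scenario, so its standard error is about 2 percentage points.

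*Drink delay, limited to 0–48 hours by eligibility.* If delay is uniform, with share c on one side of the cut, kept = 3c(1 − c).

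- c = 50% (cut at the midpoint, 24 hours): 0.75 kept, 25% lost; power Φ(2.80 × 0.866 − 1.96) = 68%.
- c = 20%: 0.48 kept, 52% lost.
- c = 10%: 0.27 kept, 73% lost.

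The last two rows show what a lopsided split costs. If delay is instead exponential in shape with share p above the cut, kept = p·(ln p)²/(1 − p), a loss of 35–52% for p between 10% and 50%.

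*Nutrition.* The result depends on a choice the protocol does not state: no loss if the score is used, about 21–24% with three categories (thirds, or 50/30/20, on a normal scale), and 36–66% with two groups and 50% down to 10% at risk.

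**What the documents do not supply.** They give no distribution of age, delay or nutrition score and no CDAD rate, so no power was computed for CDAD. If the sub-group analysis is run within each arm, n is 162, but the percentage loss is the same.

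**The case against.** The strongest reply is that the information need not be lost at all. Section 7.4 plans a logistic regression before it adds the sub-groups, and nothing there prevents continuous terms. Coding of covariates is commonly left to the SAP, so silence about it is not a fault. This stands: it is not established that the trial tests only the two-way splits. What remains is that the only coding the protocol fixes for age and delay is the split, unexplained, in the only analysis that names these factors.

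A reader might infer that nutrition is dichotomised too, so that the undernutrition objective is compromised. The documents do not support that. Section 7.4 states no nutrition cut, and the instrument yields a score, so the loss could be nil.

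A reader might also infer a fixed loss, such as 25–60% on every factor. That is not supported either: with no distributions given, the figures above run from 25% to 73% for delay and 36% to 78% for age. All assume a linear effect; if risk steps up near the cut, the split need not be inefficient.

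Two further replies have weight. Age in years is very likely held, but delay in hours is an inference: Appendix 2 lists no dose or drink times, and the drink is given once daily at a drug round, so timing may be coarse. And cuts fixed in advance prevent data-driven choice, which is a reason to keep them as descriptive sub-groups.

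**Conclusion.** The point holds for age and, where times are recorded, for drink delay. The protocol fixes an unexplained two-way split for each and does not say that the planned regression uses the underlying values. With a roughly linear effect on the log-odds and normal age, the split loses about 36% of the information if half the patients are 65 or over, 57% if 15% are, and 78% if 5% are. For delay uniform over 0–48 hours it loses about 25%, and more if lopsided. These are consequences of assumed distributions, not facts about this trial.

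For nutrition, no split is shown; the fix below only makes the use of the score explicit. It would also go too far to say that the trial will wrongly report no association, since the regression may recover what the sub-groups miss. The primary comparison and the 162/180 per-arm sample size are untouched. This is a cheap improvement to supportive analyses.

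**What to change.** In section 7.4, or in the SAP with a reference from it:

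- Enter age in years and, where both times are recorded, the time from first antibiotic dose to first drink as continuous terms in the planned logistic regression, each with a simple check for non-linearity (for example, a quadratic or spline term).
- Enter the SNST score as recorded, not as a two-group split.
- Keep 65 years or over, and 0–24 against more than 24–48 hours, worded as exclusive groups, as descriptive sub-groups.

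The cost is a sentence or two. Age and the nutrition score should need no new data collection; whether delay can be used depends on whether dose and drink times are recorded. The small downside is that a smooth shape is assumed and has to be checked.
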